## Abstract

**Background:**

Despite biomedical advances and intervention efforts, rates of preterm birth and other adverse outcomes in the United States have remained relatively intransigent. Evidence suggests that group prenatal care can reduce these risks, with implications for maternal and child health as well as substantial cost savings. However, widespread dissemination presents challenges, in part because training and health systems have not been designed to deliver care in a group setting. This manuscript describes the design and evaluation of *Expect With Me*, an innovative model of group prenatal care with a strong integrated information technology (IT) platform designed to be scalable nationally.

**Methods/Design:**

*Expect With Me* follows clinical guidelines from the American Congress of Obstetricians and Gynecologists. *Expect With Me* incorporates the best evidence-based features of existing models of group care with a novel integrated IT platform designed to improve patient engagement and support, enhance health behaviors and decision making, connect providers and patients, and improve health service delivery. A multisite prospective longitudinal cohort study is being conducted to examine the impact of *Expect With Me* on perinatal and postpartum outcomes, and to identify and address barriers to national scalability. Process and outcome evaluation will include quantitative and qualitative data collection at patient, provider, and organizational levels. Mixed-method data collection includes patient surveys, medical record reviews, patient focus groups; provider surveys, session evaluations, provider focus groups and in-depth interviews; an online tracking system; and clinical site visits. A two-to-one matched cohort of women receiving individual care from each site will provide a comparison group (*n* = 1,000 *Expect With Me* patients; *n* = 2,000 individual care patients) for outcome and cost analyses.

**Discussion:**

By bundling prevention and care services into a *high-touch, high-tech* group prenatal care model, *Expect With Me* has the potential to result in fundamental changes to the health care system to meet the “triple aim:” better healthcare quality, improved outcomes, and lower costs. Findings from this study will be used to optimize the dissemination and effectiveness of this model.

**Trial registration:**

ClinicalTrials.gov, NCT02169024. Retrospectively registered on June 18, 2014.

## Background

Birth outcomes are a nationwide health improvement priority [1]. Nearly four million women in the United States give birth each year, and 84% will give birth in their lifetimes [2, 3]. Despite substantial biomedical advances and intervention efforts, rates of preterm birth (9.6%) and low birthweight (8.1%) in the United States have remained relatively intransigent over the past three decades [4] and are considerably higher than rates in all other developed nations [5]. Extreme racial and ethnic disparities persist in the prevalence of preterm birth and low birthweight as well as consequent infant mortality. Compared to non‐Hispanic White women, Black women are about 50% more likely to deliver preterm and 90% more likely to deliver a low birthweight infant [4]. Infant mortality due to preterm or low birthweight is 3.5 times higher for Black women and nearly two times higher for Puerto Rican women, compared to non-Hispanic White women [6].

The financial and human costs associated with preterm and low birthweight babies are profound. These adverse birth outcomes account for 36% of all US infant deaths [7], and are associated with greater infant and childhood morbidity as well as increased health care costs. Complications of preterm birth include neurodevelopmental disabilities, school and behavioral problems, visual and hearing impairment, cardiovascular and metabolic disorders, and higher risk of preterm in the next generation [8, 9]. Low birthweight is associated with subsequent risk of coronary heart disease, hypertension, and diabetes [10], and has been linked to all-cause mortality among women, and premature death among men [11]. In 2005, the annual economic burden associated with preterm birth in the US exceeded $26 billion [12]. Based on health care inflation from 2005 to 2015 [13], we estimate that these costs now would exceed $38 billion. Employers pay an average of twelve times more for newborn medical care for a preterm birth than for a healthy, full-term baby in the first year of life [14]. Families incur direct medical and non-medical (e.g., special education) costs, as well as indirect costs (e.g., lost productivity). Moreover, preterm birth and low birthweight result in substantial emotional distress for parents who must advocate and make healthcare decisions for fragile newborns [15].

Preventive interventions to address preterm and low birthweight include quality improvement efforts to eliminate early elective deliveries, smoking cessation, limiting multiple embryo transfer for in-vitro fertilizations, progesterone therapy to help sustain pregnancies among women with prior spontaneous preterm birth, and cervical cerclage for women with short cervical lengths [16]. However, the causes of preterm birth are not well understood, and as many as two-thirds of preterm births have unknown etiologies [17]. Group prenatal care, involving shared medical visits among pregnant women, has been suggested as one way through which substantial improvements in birth outcomes may be achieved [18–21].

In group prenatal care, a credentialed prenatal provider (e.g., obstetrician, midwife) provides pregnancy care to eight to twelve women simultaneously during up to ten 90–120 min group visits, and follows American Congress of Obstetrics and Gynecology (ACOG) guidelines. These group sessions integrate pregnancy health assessments with additional education, skills building and peer support.

A recent meta-analysis concluded that group prenatal care was associated with a decreased rate of low birth weight overall and a reduction in risk for preterm birth for African American women, compared to individual care [22]. Significant clinical, methodological, and statistical heterogeneity between available studies limited the authors’ ability to assess other outcomes. However, the studies Carter and colleagues deemed to be the most rigorous (i.e., two NIH-funded randomized controlled trials from our research group) documented that, compared to standard individual care, group prenatal care results in lower rates of preterm and small for gestational age babies, less incident sexually transmitted infections, healthier maternal weight trajectories, and fewer depressive symptoms as well as increased patient satisfaction with care [18, 21, 23–25]. These improved outcomes may be due to reduced stress and increased knowledge, motivation, and health care engagement, resulting from the additional education and support that group prenatal care patients received [26]. More research is needed to replicate the effects of group prenatal care on perinatal and postpartum outcomes, and to identify potential mechanisms through which group prenatal care impacts health.

Estimated cost savings associated with group prenatal care (due to improved outcomes) varies by geography, ranging from $750 to $890 per birth [27]. Currently, such savings are realized by payors, such as Medicaid and private health insurers—not clinical health systems providing care. According to analyses conducted by Optum (UnitedHealth Group), if one-half of pregnant women enrolled in Medicaid received group prenatal care, net savings to Medicaid would be approximately $12 billion over the next decade [28]. A recent study aimed at determining Medicaid costs savings associated with a group prenatal care program in South Carolina documented a $2.3 million return on investment, with an average savings of $22,667 in health care expenditures for every preterm birth prevented [29].

Despite the potential for improved outcomes, group prenatal care currently is available to an estimated 3% of pregnant women in the United States [30]. Although evidence suggests that, if given a choice, approximately 50% of women would choose to participate in group care [31], widespread dissemination of group prenatal care presents challenges. First, any disruptive innovation is likely to face challenges and resistance from complex systems, such as the healthcare system, which seek homeostasis [32]. Second, the healthcare system was not designed to provide patient care in groups (i.e., infrastructure: group space, information technology systems for patient scheduling, provider scheduling, charting). Providers have not been trained to deliver care in groups (e.g., group facilitation skills, providing 20 h of patient education per pregnancy). Providers are conditioned to keep new patients for continuity of care, not refer them to the provider starting the next new prenatal group, where they will receive the remainder of care (e.g., loss of billable hours, turf issues).

Transitioning a health system from individual to group prenatal care is a challenging task that requires an organizational culture that supports innovation, one or more champions who will lead change efforts, and buy-in from administrators, clinicians, and staff [33, 34]. Moreover, a financial paradox exists whereby the healthcare delivery system bears the burden of transformation to provide group care, yet it is often not the financial beneficiary of outcome improvements. Often, prenatal clinics pay start-up (e.g., training) and ongoing (e.g., materials, accreditation) costs to deliver group prenatal care. However, much of the cost savings come from averted (or shorter) neonatal intensive care unit stays or reduced emergency department visits; those savings are not channeled back to prenatal clinics, but rather are realized by other departments or payors.

To promote more widespread adoption and sustainability of group prenatal care, we developed an innovative model of group prenatal care with a novel information technology (IT) platform, called *Expect With Me. Expect With Me* group prenatal care was designed to be scalable nationally at lower cost to clinical practices and healthcare systems through the use of technology and the engagement of payors. Since February 2014, *Expect With Me* has been implemented with more than 1,000 women in five sites in Nashville TN, Detroit MI, and McAllen TX. This paper describes the design of the intervention and evaluation plan to assess its implementation and impact on health care quality, outcomes, and costs.

## *Expect With Me* group prenatal care

*Expect With Me* group prenatal care was designed based on: (1) principles of group care [35]; (2) evidence from randomized controlled trials demonstrating improved birth outcomes for women receiving prenatal care in a group format [18, 21]; (3) clinical guidelines for prenatal care delivery [36]; and (4) research on patient and provider engagement through social media and technology [37–39]. Designed with national dissemination as a primary consideration, *Expect With Me* incorporates the best evidence-based aspects of existing models of group care [22, 40–42] with a novel IT platform to improve patient engagement and support, enhance health behaviors and decision making, connect providers and patients, and improve health service delivery.

*Expect With Me* provides care to groups of 8–12 women of the same gestational age. Women receiving *Expect With Me* begin prenatal care in the traditional manner. Formal intake (history, exam) is performed at an initial visit prior to group assignment. All prenatal care thereafter occurs within a group setting, except for health issues that require privacy and cervical assessments in late pregnancy. Ultrasounds and laboratory screenings occur per ACOG clinical guidelines [36]. *Expect With Me* is implemented from week 14 of pregnancy (after initial individual assessment) through delivery, following the same schedule as individual care. However, group visits are 90–120 min each, and follow a unique structured curriculum that incorporates the standard content of prenatal care, and emphasizes critical contemporary health issues relevant to pregnancy, such as nutrition, physical activity, stress/mental health, and sexual health. Table 1 summarizes the timing and recommended topics to be covered during each session. Participants may bring their partner, family member, or other support person to group sessions.

**Table 1 Tab1:** *Expect With Me* group prenatal care session timing and topics

Session	Themes	Topics
1 (13–17 weeks)	You’re a healthy mom	• Eat and live healthy for you and your baby • Stay active while you’re expecting • Maintain healthy weight during pregnancy • Understand routine prenatal testing and emergencies • Know what blood pressure and weight numbers are healthy for you
2 (17–21 weeks)	Staying healthy and strong through change	• How babies grow and develop • Mom’s clean teeth = healthier mother and baby • Learn why you’re feeling the way you do • Move safely and comfortably while pregnant • Get a good night’s sleep • Keep calm and stress-free while expecting • Stay safe at home, work and play
3 (21–24 weeks)	Breastfeeding = Healthy Babies and Healthy Moms	• Benefits of breastfeeding • Barriers to breastfeeding • Basics of breastfeeding • Choose a pediatric provider (Part 1) • Your support systems (Part 1)
4 (25–29 weeks)	Healthy moms building healthy relationships	• Understand Gestational Diabetes Testing • Build healthy relationships • Prevent STDs including HIV (Part 1) • Choose when to get pregnant (Part 1)
5 (27–31 weeks)	Healthy moms and healthy labor	• Signs of labor • Stages of labor (Part 1) • Fetal heart rate monitoring • Stay comfortable during labor • Understand Cesarean birth
6 (29–33 weeks)	Healthy labor	• Stages of Labor (Part 2) • What happens immediately after delivery • Labor and delivery decisions • Provider policies and options for labor and delivery • Prevent STDs including HIV (Part 2)
7 (31–35 weeks)	Healthy labor and healthy relationships	• Prepare for hospital stay and return home • Negotiate to build healthy relationships • Understand Group B Strep testing and prevention
8 (33–37 weeks)	Taking care of mom and baby	• Caring for your baby • Choose a pediatric provider (Part 2) • Care for your postpartum body • Set goals to build healthy relationships (Part 1)
9 (35–39 weeks)	Preparing for a Healthy Future	• How to breastfeed • Staying healthy and strong after pregnancy • Signs of postpartum depression • Make sure your home is safe you and your baby
10 (37+ weeks)	Build a healthy future	• Choosing a daycare provider • Going back to work • Your support systems (Part 2) • Choose when to get pregnant again (Part 2) • Set goals for a healthy relationship (Part 2)

In a group setting, credentialed prenatal providers (e.g., obstetrician, midwife) conduct one-on-one assessments with each patient (30 min) and then facilitate group discussions on the topics of pregnancy, using adult learning principles (60–90 min). Facilitated discussions allow patients to provide and receive peer support while gaining knowledge and skills related to explicit learning objectives on pregnancy, childbirth, and parenting [43]. *Expect With Me* meets a broader set of needs for pregnant women (e.g., medical, social, educational) than traditional care; yet, it is fully reimbursable by health insurance programs as prenatal care. Further, women access the IT platform during their prenatal visit to track their own health metrics (e.g., weight, blood pressure, visit attendance). This encourages patient engagement in self-care and introduces them to the online experience of care that will continue throughout their pregnancy and postpartum.

*Expect With Me* has a novel, HIPPA-secure, integrated IT platform that enables patients to track their own health metrics, communicate with health providers and fellow group patients, access healthcare resources and educational materials, provide and gain support (Fig. 1). It is optimized for use on smartphones and computers, with all content available in English and Spanish via a single toggle. Personalized profiles allow patients to log vital signs (i.e., blood pressure, weight) during prenatal visits and to view their own weight trajectory across pregnancy. It also prompts them to track health behaviors (e.g., taking prenatal vitamin, drinking water, exercising) when they log in. Patients can access educational materials, including videos, tip sheets, audio files with relaxation/mindful meditation exercises, and links to online resources. Women can journal about their pregnancy experience, send messages to other women in their group, participate in discussion board conversations, and send out birth announcements.

**Fig. 1 Fig1:**
[figure not shown]
*Expect With Me* IT platform: Select patient views (all patient names and photographs are fictional)

*Expect With Me’s* integrated information technology platform has numerous features to ease clinical implementation and aid practice management. All facilitator and patient handbooks are available electronically in both English and Spanish, eliminating the need for costly printing of materials. Prenatal care providers can use the IT platform to monitor attendance, upload and distribute educational materials to patients between visits, document care/content delivered, identify patient needs, and plan targeted care, such as inclusion of an HIV counselor or nutritionist in the next session. A scheduling tool is available to aid the establishment group care schedules that account for provider time, group space, clinic schedules, holidays and more. Health systems have access to real-time data on patient demographics and adherence, to monitor and evaluate implementation success (Fig. 2).

**Fig. 2 Fig2:**
[figure not shown]
*Expect With Me* IT platform: Select clinician views

## Development of *Expect With Me*: theoretical basis and formative research

*Expect With Me* was developed by a transdisciplinary team of researchers at Yale University, representatives from UnitedHealth Group, and health care providers at Vanderbilt University Medical Center. It is based on principles of group care, which assert that care is most effectively and efficiently provided in groups, that learning and support are enhanced, and that this high quality of care is difficult to achieve within the traditional structure of individual examination room visits [35, 44, 45]. Group prenatal care provides substantially more contact with providers (from two hours across pregnancy in individual care to 20 h in group), provides support services, and is integrated to respond to complex needs of pregnant women. Advantages of group interventions include, but are not limited to: improved learning and skills development, attitude change and motivation, enhanced insight through sharing of common experiences, and social support [43, 46]. In turn, groups facilitate development of new community norms for health-enhancing behaviors.

*Expect With Me* was designed using a human-centered design approach. Human-centered design is an iterative and participatory process to help ensure innovations are acceptable, usable, and meet the needs of users [47]. This approach has been used to shape healthcare to meet the multiple levels of need of clinicians and patient populations [48–51]. A series of key informant interviews with twenty prenatal care stakeholders and observational data collection during prenatal care visits were conducted, from which two important findings emerged. First, the healthcare industry historically has defined prenatal care in medical terms, and an important value proposition of group prenatal care is that it provides a context in which other basic, safety, and social needs can be addressed. Second, pregnancy provides an opportunity to re-evaluate how those needs are being met, and prenatal care messaging would benefit by moving from a frame of fear and avoidance (e.g., what not to eat, drink, and do) to embracing good health habits for women and their families. An independent team of four curriculum development and writing professionals were commissioned and—following clinical guidelines from the American Congress of Obstetricians and Gynecologists and best practices for group facilitation—developed a ten-session structured curriculum and supplemental materials for the IT platform, grounded in the lessons learned during this process. To ensure accuracy, relevance, and feasibility, all content associated with *Expect With Me* (e.g., facilitator and patient handbooks, tip sheets and other resources) was reviewed by a medical team, including obstetricians/maternal-fetal medicine specialists, midwives, and pediatricians). A pilot study of *Expect With Me* was conducted with 243 pregnant women in Nashville TN; based on this pilot, revisions were made to enhance structure and content of the curriculum. The result of this extensive formative research is a supportive, comprehensive model of group prenatal care that aims to identify and address the full spectrum of pregnant women’s needs throughout pregnancy and beyond, fostering long-term health for women and their families.

## Methods/Design

*Expect With Me* is being evaluated via a multisite, longitudinal matched-cohort study, in which data are collected in a real-world settings at the patient and organizational levels. For national scale-up and sustainability, it is essential that the program not only be effective for patients but that the implementation strategy fits with the context of health clinics providing prenatal care [52]. A rigorous multi-method evaluation is being conducted to examine the impact of *Expect With Me* on maternal health and birth outcomes and identify and address barriers to national scalability. Cost analyses are also planned.

The study includes a rigorous process and outcome evaluation. Birth outcomes are the primary study outcomes (e.g., preterm birth, birthweight, neonatal intensive care unit admission/duration). Maternal psychosocial, health behaviors, and health outcomes (e.g., depression, breastfeeding, postpartum weight loss) are secondary outcomes.

The process evaluation will identify factors that influence uptake, fidelity, and sustainability of *Expect With Me* to inform scalability. We will employ quantitative approaches, such as online surveys and health record reviews as well as systematic qualitative approaches, such as in-depth interviews and focus groups. Key components of comprehensive process evaluations specified by Steckler and Linnan [53] will be adapted to meet the specific needs of this study. Uptake will include reach (number of groups offered); dose delivered (extent to which providers enroll patients and facilitate *Expect With Me* sessions); and dose received (willingness of eligible patients to participate; attendance in group sessions). Fidelity refers to the quality and integrity of the intervention as conceived, and is a function of implementation by clinical sites. We will examine how groups were planned and populated, the content and process of each session, and the perceptions of site staff and patients about *Expect With Me*. We will document whether *Expect With Me* patients received the intended exposure to the intervention, including attendance at each session; proportion of prenatal visits delivered in group; and patient use of IT platform. Sustainability will be driven, in part, by the impact of *Expect With Me* on healthcare costs. We will analyze the impact of birth outcomes on healthcare costs. We will document differences in utilization of care (e.g., emergency department, neonatal intensive care unit) between *Expect With Me* and individual care. Sustainability is impacted by depth of training and satisfaction with *Expect With Me* by providers and staff. We will document penetration of staff trainings and collect feedback from clinical site personnel. These data can be used to scale this intervention, nationally.

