## Analyses

Descriptive analyses of quantitative data will be performed. Women who participated in group prenatal care and those who received individual care will be matched on the basis of propensity scores. Propensity score matching is a statistical technique to correct for observable difference between the treated and non-treated group, thereby reducing selection bias and strengthening causal inferences, in observational studies [60]. We will use multiple imputation and maximum likelihood techniques to handle missing data and sensitivity analyses to assess the robustness of inferences about treatment effects to various missing data assumptions, as needed.

Generalized linear and logistic regression models will be used to analyze continuous (e.g., gestational age at delivery and birth weight) and dichotomous outcomes (e.g., preterm birth, low birth weight), respectively. Negative binomial regression models will be used to analyze count outcomes (e.g., neonatal intensive care unit days). Each model will include a main effect for treatment group (*Expect With Me* vs. individual care). Because many women who attend group prenatal care sessions also supplement with individual visits [61], adjusted models will control for number of individual visits, as well as contain predictor variables that are clinically meaningful to a specific hypothesis of interest.

Trajectories of change for outcomes that are repeatedly measured over time (e.g., weight) will be examined using linear and non-linear mixed effects modeling, with a random effect for subject. An optimal covariance structure will be selected based on the likelihood ratio test for nested models and based on the Akaike Information Criterion for non-nested models [62]. The main independent effects of time, treatment, and second-degree interactions of these predictors will be considered in each model, adjusting for other covariates as described above.

Multilevel mixed models will be used to identify factors that influence primary outcomes among *Expect With Me* patients, with the effect of site modeled as a random effect. A scale variable that will reflect a woman’s attendance level at prenatal care group visits will be created to evaluate whether there is a “dose–response” intervention effect. Structural equation models will be used to examine factors that may mediate the relationship between participation in group care sessions and improved outcomes.

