## Sample size

Results from previous randomized controlled trials suggest that group prenatal reduces likelihood of delivering a preterm or small for gestational age baby by 33–34% [18, 21]. Based on these findings and the national preterm birth rate of 9.6% [4], we need a minimum of 1,768 study participants with one-third (*n* = 884) receiving group prenatal care to have power of .80 to detect differences at alpha = 0.05 with a one-tailed test. With a potential 10% drop out rate due to miscarriage, pregnancy complications and changes in life circumstances (e.g., geographic move), we will recruit 1,000 women, expecting to follow more than 900 of them through one-year postpartum. We will compare primary maternal health and birth outcomes for these women with a 2–1 matched cohort of 2,000 patients receiving individual care. Therefore, the total study sample of women receiving both group and individual prenatal care will include a total of 3,000 women.

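### The primary outcome is an open list of birth outcomes, while the study is sized on preterm birth alone and the text disagrees on whether maternal health is primary

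*Protocol article*

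**What the plan says.** Methods/Design is the only place where the article defines the primary outcome: "Birth outcomes are the primary study outcomes (e.g., preterm birth, birthweight, neonatal intensive care unit admission/duration". Read item by item, this names four outcomes: preterm birth, birthweight, NICU admission and NICU duration. The next sentence sets the boundary on the maternal side: "Maternal psychosocial, health behaviors, and health outcomes (e.g., depression, breastfeeding, postpartum weight loss) are secondary outcomes".

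The Sample size section takes a 33–34% relative reduction from previous randomised trials and one event rate: "Based on these findings and the national preterm birth rate of 9.6" per cent. It gives one alpha of 0.05, described as one-tailed, with power 0.80. It then says: "We will compare primary maternal health and birth outcomes for these women".

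The Analyses section plans regressions by type of variable: "continuous (e.g., gestational age at delivery and birth weight) and dichotomous outcomes (e.g., preterm birth, low birth weight), respectively". For counts: "Negative binomial regression models will be used to analyze count outcomes (e.g., neonatal intensive care unit days". On testing it adds: "Each model will include a main effect for treatment group". It gives no order among the outcomes and no rule linking them to a conclusion.

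**The concern.** Three statements do not fit together. Primary status goes to a category with examples, the sample size and error rate are set for one member of that category, and maternal health is secondary in one section and primary in another. A reader of the final report could not tell from this article which result the study stood or fell on.

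At stake is the meaning of the nominal error rate. It holds for one pre-named test. If the headline can be taken from several treatment effects, the chance that at least one favours group care by luck is higher. Pre-specification matters more here because the comparison is a non-randomised matched cohort, the study was registered retrospectively, and the findings are meant to guide wider dissemination.

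**Working it through.** **1. Which outcome the sample size rests on.** Inputs from the Sample size section: comparison rate p1 = 0.096, reduction 33%, power 0.80. The 2:1 ratio is also stated under Organizations and study population.

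- p2 = 0.096 × 0.67 = 0.06432; difference d = 0.03168.
- Pooled rate at 2:1: (0.06432 + 2 × 0.096)/3 = 0.08544.
- Group-care n = [z_α √(1.5 × 0.08544 × 0.91456) + z_β √(0.06432 × 0.93568 + 0.096 × 0.904/2)]² / d².
- The square roots are 0.34236 and 0.32183. With z_α = 1.960 (two-sided 5%) and z_β = 0.8416, n = 883.9, so 884 in group care and 1,768 in individual care.

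These are exactly the two numbers printed in the article. The calculation therefore uses preterm birth alone, as one test. (The match is to a two-sided test with 1,768 as the comparison arm, whereas the text says one-tailed and treats 1,768 as the total. That is a separate matter, but it leaves open which sidedness the analysis will use, so both are shown below.)

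**2. Error rate if four named outcomes are each tested at an undivided level.** Let k = 4. The documents give no correlation between the test statistics; the values of ρ below are assumptions, with one common ρ.

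- Independent: 1 − (1 − a)^k.
- Correlated: 1 − P(all four standard normals with common correlation ρ fall below the critical value).

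The second column gives the chance of at least one false positive with one-tailed 5% tests. The third gives the chance of at least one false claim of benefit with two-sided 5% tests, which is 2.5% per test in that direction.

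| Assumed ρ | One-tailed 5% each | Two-sided 5% each, benefit only |
|---|---|---|
| 0 | 1 − 0.95⁴ = 18.5% | 1 − 0.975⁴ = 9.6% |
| 0.5 | 14.4% | 7.8% |
| 0.7 | 12.0% | 6.5% |
| 0.8 | 10.6% | 5.7% |
| 0.9 | 8.8% | 4.7% |

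Against the single-test rates of 5% and 2.5%, the multiple runs from 3.7 to 1.8 (18.5/5 to 8.8/5) and from 3.9 to 1.9 (9.6/2.5 to 4.7/2.5).

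**3. What each remedy does to the sample size (33% reduction).**

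- Preterm birth as single primary: 884 + 1,768 gives 80.0% power two-sided or 88.0% one-sided. No change in N.
- Four co-equal primaries with alpha 0.05/4 = 0.0125: power for preterm birth at 884 + 1,768 falls to 60.6% two-sided or 70.6% one-sided. At the planned 1,000 + 2,000, before dropout, it is 67.6% or 76.7%. Restoring 80% needs about 1,264 + 2,527 two-sided or 1,075 + 2,149 one-sided, before dropout, both above plan.

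**4. Maternal outcomes.** Methods/Design classes maternal health outcomes as secondary; Sample size groups them with birth outcomes under the word primary. Both cannot hold.

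**The case against.** A reader might infer that the plan allows success to be declared on any birth outcome at the full 5% level. The article does not say so. Alpha appears only as an input to the sample-size calculation, the Analyses section gives no level or success rule, and multiplicity control is commonly left to an analysis plan, which is not shown. Its absence here is therefore not the finding. The open list may also be condensation of a fuller protocol. This limits the point to what the article fails to prevent. It does not remove the conflict between a plural, open definition and single-outcome sizing, or the contradiction over maternal health.

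A second tempting reading is that the false-positive rate is simply three times nominal. That needs one-tailed testing and a correlation near 0.5. NICU admission is NICU days above zero, and preterm birth and birthweight are closely linked, so higher correlations are plausible and 18.5% is an upper figure for four one-tailed tests. This stands, and the range is given accordingly.

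Third, gestational age and low birth weight appear under Analyses only as examples of variable types and are not called primary, so they are not counted.

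Finally, several primary outcomes can be legitimate if the list is closed and the error controlled, and family-wise error is a weaker concern in an observational cohort with implementation aims than in a confirmatory randomised trial. That is fair and bears on the weight of the point. Knowing which result is the headline still matters in such a cohort.

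**Conclusion.** The point holds in limited form. The article fixes its primary outcome badly: it is an open category in one section and a single sized outcome in another, with maternal health on both sides of the line. As written, nothing in it stops the headline from being chosen among several tests; it does not state that this will be done.

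The possible size, for four named outcomes tested without adjustment, is 18.5% down to 8.8% with one-tailed 5% tests and 9.6% down to 4.7% for a false claim of benefit with two-sided 5% tests, over assumed common correlations from 0 to 0.9. These figures are conditional on the number of tests, the assumed correlations, the sidedness and the absence of a multiplicity rule elsewhere. This should be corrected; it does not invalidate the design.

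**What to change.** Name preterm birth, the outcome the study is sized on, as the single primary outcome, and state its gestational-age cut-off, which the article does not give. List birth weight, NICU admission, NICU days and any other birth outcomes as secondary, either tested in a fixed order after preterm birth or reported as estimates with 95% confidence intervals. In the Sample size section, correct the wording that calls maternal health outcomes primary so that it agrees with Methods/Design.

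The cost is mainly wording, and N is unchanged. The other birth outcomes lose primary status. Because the study is registered and under way, with more than 1,000 women already in the programme, the change must be dated, justified and made before outcome data are analysed. Keeping four co-equal primaries is possible but would require a closed list and a divided alpha, with the loss of power shown above.
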